### Collaborators and setting

The FAIR study is being conducted by the National Institute for Medical Research (NIMR) in Tanzania, the University of Oxford, CWBSA, and Pact Tanzania. The study will be conducted in eight districts of rural and semi-urban Tanzania: Kyela District Council (DC), Mbeya DC, Muleba DC, Shinyanga DC, Shinyanga Municipal Council, Kahama Town Council, Msalala DC, and Ushetu DC. PLH-Teens will be delivered by teachers in schools and in communities by volunteers (compensated with an honorarium) (*N* = 444) with Furaha program coaches (*N* = 70) providing facilitators with ongoing supervision. Facilitators will deliver the program via the coordination of five LIPs—Humuliza, Tadepa, Integrated Rural Development Organisation, Caritas, and Tanzania Red Cross Society.

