### Secondary quantitative data collection

The study will analyze the following anonymized secondary process and outcome data from Pact Tanzania and CWBSA: pre-post surveys completed by parent/caregivers (*N* = 50,000); pre-post surveys completed by adolescents (*N* = 50,000); parent/caregiver and adolescent program attendance registers (*N* = 100,000 participants); facilitator demographic questionnaires (*N* = 444); coach demographic questionnaires (*N* = 70); coach assessments of facilitators (*N* = 444); CWBSA assessments of coaches (*N* = 70); LIP organizational surveys (*N* = 5); and implementation cost surveys (*N* = 300).

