#### Implementation process measures

Pact Tanzania, LIPs, and CWBSA will collect data about parents/caregivers and adolescents (e.g., attendance), facilitators (e.g., demographic characteristics, fidelity), and coaches (e.g., demographic characteristics, fidelity) (see OSF page). The data will be used to understand the quality of program implementation, the factors that predict implementation outcomes, how implementation varies from context to context, and how implementation is associated with intervention outcomes. In particular, information about participant attendance, staff demographics, facilitator competent adherence, coach competent adherence, and organizational characteristics will be collected using a variety of measures (see Additional file 8). For example, data on facilitator competent adherence will be collected by Pact coaches using the PLH-Facilitator Assessment Tool for Teens (PLH-FAT-T)—an observational assessment tool administered by coaches based on live observations or video recordings of group sessions. Facilitator competent adherence is the skill with which a facilitator delivers intervention components and the strictness with which they follow the activities outlined in the program manual [50, 51]. All of the implementation data collected will be linked to parent/caregiver and adolescent outcomes through the use of unique identifiers supplied by LIPs, which will make it possible to link data from multiple sources. The data will be anonymized by the LIPs before it is shared with researchers.

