The level of implementation of PLH-Teens delivery will be determined by analyzing data from family attendance registers; facilitator assessments; coach assessments; structured observations of group sessions; interviews held with facilitators, coaches, and LIP staff; and FGDs held with adolescents, parents/caregivers, facilitators, and coaches. Attendance rates and attendance trends among parents/caregivers and adolescents, as well as variations in attendance, and program completion rates will be calculated based on the attendance registers to determine the extent of participation in PLH-Teens. The level of competent adherence with which facilitators deliver the program will be determined using the results from the Facilitator Assessment Tool assessments completed by coaches. To examine the reliability and validity of the Facilitator Assessment Tool, a psychometric evaluation consisting of content validity (stakeholder perspectives from interviews and focus groups with facilitators, coaches, and CWBSA staff), intra-rater reliability (percentage agreements and intra-class correlations), inter-rater reliability (percentage agreements and intra-class correlations), internal consistency (Cronbach Alphas), construct validity (exploratory factor analyses), and predictive validity analyses will be performed. Similarly, the level of competent adherence with which coaches deliver facilitator supervision will be determined using the results from the Coach Assessment Tool assessments completed by CWBSA staff. Interviews, FGDs, and session observations will be used to expand upon and contextualize the findings regarding the demographic, attendance, facilitator competent adherence, and coach competent adherence data.

#### Research question 2

Factors associated with the quality of implementation will be examined using the socio-demographic data from the Facilitator and Coach Profile Forms; LIP organizational characteristics surveys; interviews; FGDs; and structured observations of group sessions. Correlation and regression analyses will be used to examine the relationship between facilitator and coach competent adherence and their associations with family, facilitator, coach, and organizational characteristics. Interviews, FGDs, and session observations will be used to expand upon and contextualize the findings.

#### Research question 3

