### Data quality and potential biases

Collecting comprehensive assessments of family-level outcomes from 100,000 beneficiaries is challenging. As a result, the study relies on existing data collection tools and processes developed and used during program implementation by Pact Tanzania’s Monitoring and Evaluation team. If timing allows, the research team will conduct random checks to verify the quality of implementation and outcome data. Among the observational facilitator and coach assessments, CWBSA will double code a random sample of program delivery videos to verify the accuracy and reliability of the assessments. As a significant amount of study data relies on self-reports, this data could be limited by recall and social desirability bias.

Where relevant, the study will take into consideration advice regarding how to manage and analyze data with FUPS characteristics (flawed, uncertain, proximate, and sparse), such as by presenting the data flow, conducting statistical sensitivity checks, and making the analyses accessible [57]. In the event of missing outcome data on individuals who are eligible but not included in the sample, sensitivity analysis will be done by replacing missing data with simulated data.

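### Coaches assign the facilitator adherence scores that RQ2 relates to coach variables, and no coach or rater level is named, so a coach effect cannot be told from coach leniency

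*Protocol article*

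**What the plan says.** All references are to the protocol article.

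- **Supervision.** Collaborators and setting describes delivery "with Furaha program coaches (*N* = 70) providing facilitators with ongoing supervision".
- **Scoring of facilitators.** Implementation process measures says "data on facilitator competent adherence will be collected by Pact coaches using the PLH-Facilitator Assessment Tool for Teens (PLH-FAT-T"), and calls the tool "an observational assessment tool administered by coaches based on live observations or video recordings of group sessions". Under Research question 1, the level of facilitator adherence "will be determined using the results from the Facilitator Assessment Tool assessments completed by coaches". Secondary quantitative data collection lists "coach assessments of facilitators (*N* = 444").
- **Scoring of coaches.** Under Research question 1, coach adherence is determined "using the results from the Coach Assessment Tool assessments completed by CWBSA staff".
- **Use of the scores.** Research question 2 applies correlation and regression to "examine the relationship between facilitator and coach competent adherence and their associations with family, facilitator, coach, and organizational characteristics". Research question 3 relates change in family outcomes to facilitator and coach adherence and characteristics, among other variables. Families report those outcomes by questionnaire.
- **Clustering.** Quantitative analyses plans mixed models, where feasible, for parenting groups. Coach or rater is not named as a level.
- **Checks on the scores.** Data quality and potential biases says "CWBSA will double code a random sample of program delivery videos", as a check on accuracy and reliability. Research question 1 adds intra- and inter-rater agreement for the tool. Neither check is tied to the models for questions 2 and 3.

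**The concern.** The same group of people supervises the facilitators and marks them, and the marks are then analysed against properties of the markers. A generous or strict coach moves all the scores that he or she gives in the same direction. This has two consequences for question 2. First, scores given by one coach are correlated, so an analysis that counts facilitators as independent overstates its precision for any coach-level predictor. Second, if generosity goes with a coach trait such as experience or background, the scores will track that trait even when delivery does not. A parenting-group random effect absorbs neither, because the shared component sits with the coach and spans facilitators.

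The study intends to show how delivery can be improved, including through staff factors. A coach-facilitator association that reflects marking habits could be taken as evidence about coaching.

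**Working it through.** **Inputs.** From the protocol: 444 facilitators and 70 coaches. The protocol gives no power, intraclass correlation or rater variance for these analyses, so there is no figure to reproduce and the following are assumptions: leniency share of score variance L = 0.10, 0.20, 0.30; correlation ρ between leniency and a coach variable = 0, 0.3, 0.5; true adherence-outcome correlation 0.20. The simulation used 2,000 replicates per setting, with true adherence unrelated to the coach and each facilitator scored by one coach.

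**1. Facilitators per coach.** m = 444/70 = 6.34.

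**2. Question 2, leniency unrelated to the coach variable (ρ = 0).** Design effect = 1 + (m − 1)L. Effective N = 444/design effect. The approximate false-positive rate of a test that ignores coach is 2[1 − Φ(1.96/√design effect)].

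| L | Design effect | Effective N | Approximate rate | Simulated, facilitator level | Simulated, coach means |
|---|---|---|---|---|---|
| 0.10 | 1.53 | 289 | 11% | 11.8% | 4.9% |
| 0.20 | 2.07 | 215 | 17% | 17.8% | 5.5% |
| 0.30 | 2.60 | 171 | 22% | 23.0% | 5.4% |

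Here the estimate is centred on zero. The fault is in the standard error, and analysing at coach level repairs it.

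**3. Question 2, leniency correlated with the coach variable.** The expected spurious correlation is ρ√L. The smallest case is 0.3 × √0.10 = 0.095 and the largest is 0.5 × √0.30 = 0.274; the simulated means run from 0.096 to 0.272. The coach-means test, which handles the clustering correctly, still rejects in 36% (L = 0.10, ρ = 0.3) to 97% (L = 0.30, ρ = 0.5) of replicates. Only scores from someone other than the coach separate the two explanations.

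**4. Question 3.** Leniency is error in one predictor. The expected correlation is 0.20 × √(1 − L) = 0.190, 0.179 and 0.167 for L = 0.10, 0.20 and 0.30, which the simulation matches (about 0.19, 0.18 and 0.17). The raw slope per score point shrinks by 1 − L, that is to 0.90, 0.80 and 0.70 of its value. The direction is towards zero.

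**5. Why only one correction in question 3.** Centring within coach already removes a constant leniency. At L = 0.20, dividing the centred slope by 0.80 as well would multiply it by 1/0.80 = 1.25, an overstatement of 25%.

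**The case against.** The strongest reply is that this is a condensed article with open-ended methods wording. It allows structural equation models, which can represent measurement error. It promises sensitivity checks for flawed data, evaluates rater reliability, and lists researcher observation of sessions as a further source. Rater intercepts could be left to a fuller analysis plan, and nothing in the text forbids a coach level. It stands that rater reliability is examined and that a coach level is not excluded. However, the article itself fixes who scores, which associations are tested, which clustering unit is modelled and what the double-coding is for. A reliability coefficient can reveal leniency but does not take it out of a regression that still uses the coach scores. The researcher observations cover only five program sessions.

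It also stands that no section says each facilitator is scored by his or her own coach. If another coach scores, the link to the supervising coach's traits weakens, but clustering by rater remains.

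Three stronger readings are tempting and are not supported:

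- *Shared leniency by itself produces a coach-trait correlation.* It does so systematically only if leniency correlates with that trait. Coach adherence is scored by CWBSA staff, so the two adherence measures do not share a coach rater.
- *Leniency dominates the coach means, so the coefficients are mostly artefact.* The share L/(L + (1 − L)/6.34) is indeed 41%, 61% and 73% for the three assumed values of L. It describes noise in the coach means, not bias in a coefficient.
- *Leniency creates or confounds the question 3 associations.* Families report the outcomes, and the documents give no route by which a coach's marking would alter those reports.

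**Conclusion.** The point holds in a limited form. As written, the plan relates coach-assigned scores to coach variables without a coach or rater level and without using independent scores in the models. For coach-level predictors in question 2, a test that ignores coach has a false-positive rate of about 12% to 23% if leniency is 10% to 30% of score variance. If leniency also correlates 0.3 to 0.5 with a coach trait, a spurious correlation of about 0.10 to 0.27 can appear, and clustering adjustment leaves it in place. In question 3 the main effect is modest attenuation and a less clear split between coach and facilitator contributions. All leniency shares and correlations are assumptions. The own-coach assignment is an inference that the protocol should confirm or correct.

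**What to change.** 1. State who scores whom, and add a coach (rater) random intercept to every question 2 and question 3 model that uses PLH-FAT-T.
2. Repeat the question 2 associations of facilitator adherence with coach adherence and coach characteristics on the CWBSA double-coded scores. Report them beside the full-sample coach-scored results, and do not read the coach-scored association as a coaching effect unless the two agree. Because CWBSA also scores the coaches, different CWBSA raters should do the two tasks.
3. For question 3, add one sensitivity analysis: either split PLH-FAT-T into within-coach and between-coach parts, or correct for rater variance estimated from the double-coded sample. Do not do both.
4. Do not centre PLH-FAT-T within coach where it is the response in question 2, since that removes the between-coach variation under study.

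The cost is mainly analysis wording, because the double-coding is already planned. The downside is that the double-coded sample is smaller, of unstated size and limited to video-recorded sessions. Its intervals will be wider, and it may cover few facilitators per coach. Its size should be stated with this use in mind.

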### Study participants

The study will collect primary data from 48 program coaches, 96 program facilitators, 58 Pact Tanzania and LIP staff, eight school principals, three CWBSA staff, 155 parents/caregivers, and 155 adolescents. The study will also collect anonymized secondary data from approximately 50,000 parent-child dyads (*N* = 100,000), 444 program facilitators, 70 program coaches, and five LIPs. The inclusion criteria used to select study participants for primary and secondary data collection are outlined in Tables 2 and 3.

**Table 2 Tab2:** Inclusion criteria for primary data study participants

Study participant group	Primary data inclusion criteria
Program Coaches (*N* = 70)	• Attended the Furaha Teens coach training workshop; and • Provided coaching to facilitators during the implementation of Furaha Teens.
Program Facilitators (*N* = 444)	• Teachers or community volunteers; • Attended the Furaha Teens facilitator training workshop; and • Implemented the Furaha Teens program.
Pact Tanzania and LIP Staff (*N* = 58)	• Staff member working for either Pact Tanzania or one of the LIPs delivering Furaha Teens.
School Principals (*N* = 8)	• Principal in a school where Furaha Teens was delivered.
CWBSA Staff (*N* = 3)	• Staff member working for CWBSA involved in the implementation or research associated with the FAIR Study.
Parents/caregivers (*N =* 155)	• Aged 18 or older; • Primary caregiver responsible for the care of an adolescent between the ages of 9 and 14 who attended the Furaha Teens program; and • Attended in the Furaha Teens program.
Adolescents (*N =* 155)	• Aged 9 to 14; • Consent provided by primary caregiver responsible for the adolescent’s well-being; • Assent provided by the adolescent; • Primary caregiver responsible for their care attended the Furaha Teens program; and • Attended in the Furaha Teens program.

**Table 3 Tab3:** Inclusion for secondary data study participants

Study participant group	Secondary data inclusion criteria
Adolescents (*N =* 50,000)	• Adolescent girl aged 9 to 14; • Participated in the Kizazi Kipya Project; • In the same household as her parent/caregiver at least 4 days a week; • Parent/caregiver attended the Kizazi Kipya Project; • Consent provided by primary caregiver responsible for the adolescent’s well-being; and • Assent provided by the adolescent.

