#### Session observations

To better understand the implementation fidelity of PLH-Teens, researchers will conduct observations of program delivery and supervision sessions. Program participants and facilitators will be observed during program sessions (*N* = 5 sessions; 150 participants) and facilitators and coaches will be observed during supervision sessions (*N* = 5 sessions; 50 participants). The exact locations of the five program observations will be selected by the implementation team to take the variation and contextual factors of each district into consideration. A random selection of five coaching observations will be conducted in consultation with Pact Tanzania. Observations of program sessions and supervision sessions will follow structured observation guides (see Open Science Framework).

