#### Quantitative analyses

Quantitative data will be cleaned using Stata and analyzed in Stata and R using methods such as correlation and regression analyses, as well as structural equation models. The frequencies and distribution of each variable will be examined to check for any implausible values as well as to select the appropriate analysis method (e.g., a suitable regression link function). When there are more than two items in a given scale, coefficients such as Cronbach Alphas or Omegas will be used to assess the item-level reliability of the measures. Where possible, mixed effect models will be utilized to account for nesting within parenting groups [53]. Missing data will be addressed appropriately by considering the complete case observations as well as using full information maximum likelihood or multiple imputation, as appropriate [54, 55]. Where relevant, TREND guidelines will be used when reporting quantitative results [56].

#### Research question 1

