A variety of data sources will be used to examine how implementation is associated with changes in VAC and family well-being. In particular, correlation and regression analyses will be used to look at whether pre-post changes in family outcomes are associated with family attendance, facilitator and coach competent adherence, and facilitator and coach characteristics, as well as LIP characteristics. Interviews, FGDs, and session observations will be used to expand upon and contextualize the findings.

#### Research question 4

Participant and implementing staff perspectives on the acceptability, appropriateness, feasibility, benefits, and challenges of delivering PLH-Teens in their communities will be examined by analyzing the interviews, FGDs, and session observations with school principals, facilitators, coaches, LIP staff, CWBSA staff, adolescents, and parents/caregivers.

#### Research question 5

Changes in VAC and participant well-being will be analyzed based on data gathered from parent/caregiver pre-post questionnaires, adolescent pre-post questionnaires, interviews, and FGDs. Multi-level models will be used to examine differences in pre- to post-intervention family-level outcomes and to compare differences in outcomes reported by both adolescents and parents/caregivers. Variation in the pre-post changes will be examined by participant baseline characteristics, and, if possible, by parenting group and LIP. The analyses will be similar to treatment-on-the-treated analyses since all participants included in the monitoring data would have engaged with the program to some extent. The levels of change reported by participants will be compared to the levels of change reported by the treatment and control groups in the randomized trial of the program in South Africa. Where possible, the reliability of the family survey items will also be examined using coefficients such as Cronbach Alphas or Omegas.

The findings from the interviews and FGDs  will also be analyzed to explore participant perspectives on the impacts of the program on them and their families. The interviews and FGDs will also reveal what impact implementing volunteers and staff assess the program had and will have on themselves, participants, schools, and communities.

#### Research question 6

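### The methods named for Research question 3 do not separate how attendance relates to change among families within a parenting group from how it relates to change between groups

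*Protocol article*

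**What the plan says.** Under Data analysis, Research question 3, the protocol article states that "correlation and regression analyses will be used to look at whether pre-post changes in family outcomes are associated with family attendance". The same sentence goes on to list "facilitator and coach competent adherence, and facilitator and coach characteristics, as well as LIP characteristics" as further predictors. It gives no model equation, and it does not say how attendance is coded or centred, or whether the predictors are entered together.

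Grouping is handled once, in the opening paragraph of Quantitative analyses: "Where possible, mixed effect models will be utilized to account for nesting within parenting groups". That statement covers the quantitative work in general and is conditional. The same paragraph lists structural equation models among the possible methods.

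Under Research question 1, attendance is to be described: "Attendance rates and attendance trends among parents/caregivers and adolescents, as well as variations in attendance, and program completion rates will be calculated". No split into variation within groups and variation between groups is named there or under Research question 3.

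**The concern.** Attendance is recorded for each participant but arises in parenting groups. Families in one group differ in how often they come. Groups also differ from one another, for example by setting, travel distance or facilitator. A correlation, or a regression on the family's own attendance, returns one number for both kinds of difference. A random intercept for group deals with non-independence, but its slope is still a weighted average of the two associations unless group effects are unrelated to attendance. That condition fails if better-run groups both keep families coming and show more change, a link that Research question 3 makes plausible.

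The distinction matters because the study aims to learn how implementation can be improved. A within-group association points towards keeping individual families engaged. A group-level association points towards delivery or context. A blended coefficient does not tell the reader which of these goes with change.

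**Working it through.** The article gives no sample size, power or significance level for Research question 3, so there is no planned figure to reproduce. The check asks how much between-group association enters a single attendance slope.

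**Inputs**

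- Families: Study participants gives "approximately 50,000 parent-child dyads (*N* = 100,000), 444 program facilitators, 70 program coaches, and five LIPs", so N = 50,000 dyads.
- Families per group, m: not stated. The only hint is in Session observations, with 5 sessions and 150 participants: 150/5 = 30 people, or about 15 dyads. This is rough, since facilitators may be among the 150. Assumed: 10, 15 and 30.
- Share of attendance variance lying between groups, a: not stated. Assumed: 0.05 to 0.4.
- Group ICC of outcome change, r: not stated. Assumed: 0.02 to 0.2.
- Correlation between a group's attendance level and its change, ρ: not stated. Assumed: 0.1 to 0.3.

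**Step 1: formula.** Scale attendance and change to variance 1. The within-group part of attendance is W = (1 − a)(m − 1)/m. The variance of observed group means is B = a + (1 − a)/m, and W + B = 1. Let ψ = (1 − r)/(1 − r + m·r). The random-intercept slope gives weight ψB/(W + ψB) to the between-group slope. A plain correlation or ordinary regression gives it weight B.

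**Step 2: one case (m = 15, r = 0.05, a = 0.2).**

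- W = 0.8 × 14/15 = 0.747
- B = 0.2 + 0.8/15 = 0.253
- ψ = 0.95/(0.95 + 0.75) = 0.559
- Between-group weight with a random intercept: 0.559 × 0.253/(0.747 + 0.142) = 0.16
- Between-group weight without one: 0.25

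**Step 3: range.** At m = 15 and r = 0.05:

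| a | with random intercept | without |
|---|---|---|
| 0.05 | 0.07 | 0.11 |
| 0.1 | 0.10 | 0.16 |
| 0.2 | 0.16 | 0.25 |
| 0.4 | 0.31 | 0.44 |

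Over all the values tried, the weight runs from 0.01 (m = 30, r = 0.2, a = 0.05) to 0.41 (m = 10, r = 0.02, a = 0.4) with a random intercept, and from 0.08 to 0.46 without one.

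**Step 4: the slope when the within-group association is zero.** Use the case in Step 2 with ρ = 0.3.

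- Group covariance: 0.3 × √(0.2 × 0.05) = 0.03
- Slope on the observed group mean: 0.03/0.253 = 0.118
- Random-intercept slope: 0.118 × 0.159 = 0.019 SD per SD
- Pooled correlation: 0.03
- Standard error of the random-intercept slope: √[0.95/(50,000 × 0.888)] = 0.0046
- z = 0.019/0.0046, about 4.1

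With ρ = 0.2 the slope is 0.0126 (z about 2.7), and with ρ = 0.1 it is 0.0063 (z about 1.4). A simulation of 3,333 groups of 15 (50,000/15), with 200 data sets per setting, agrees. At the two-sided 5% level the single slope was significant in 99%, 82% and 27% of runs for ρ = 0.3, 0.2 and 0.1. The within-group term was significant in about 4 to 5%.

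**Step 5: does the split work?** A separate simulation used 400 groups of 15, with 15 runs per setting, a true within-group slope of 0, a slope of 0.5 on the group's underlying attendance level, and group variance 0.05. The single term averaged 0.027, 0.052 and 0.095 for a = 0.1, 0.2 and 0.4. After the split, the within-group coefficient averaged −0.001, 0.002 and −0.002, and the group-mean coefficient 0.32, 0.39 and 0.46.

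**The case against.** A reader might infer that the plan enters attendance as one variable in a group random-intercept model and will report the slope as a family dose effect. The article does not support that. It fixes no coding, and attendance comes from separate parent/caregiver and adolescent registers, so even a single attendance variable is an inference. The group effect is general and conditional, not a stated part of the Research question 3 model. The text speaks of association and never of dose.

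Other points on that side:

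- Splitting a covariate into group mean and deviation is model detail that a condensed article often leaves to a fuller document, which is not shown here. This stands as a reason to treat the point as an improvement rather than an error. It does not remove the point, because correlation is a named method and cannot make the distinction.
- Delivery is also measured directly, through the facilitator, coach and LIP variables in the same sentence. If these are entered jointly with attendance, part of the group-level difference is removed. Joint entry is not stated, and measured covariates would leave unmeasured differences such as travel distance. The simulations include none of these covariates, so they may overstate the blend.
- The slope in the worked case is small, and its significance reflects the number of families. This stands.
- The split does not identify a lever for action. Families choose how often to attend, and a group mean reflects composition and setting as well as delivery. This also stands and limits how both coefficients may be described.

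**Conclusion.** The point holds as a modest, inexpensive improvement, not as a demonstrated error. The methods named for Research question 3 do not separate within-group from between-group association of attendance with change, and the conditional mixed models reduce the blend without removing it.

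Its size cannot be determined from the article. Under the assumed group sizes and ICCs it runs from negligible to moderate. The 0.019 SD per SD result rests on 15 families per group, attendance ICC 0.2, change ICC 0.05, a group-level correlation of 0.3 and no adjustment for delivery measures. A slope that small means little in substance, but with about 50,000 dyads it can easily look significant. That is why the coefficient should be labelled by level.

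**What to change.** State that the Research question 3 mixed model enters attendance as two terms: the parenting-group mean, and the family's deviation from that mean. Include them alongside the listed facilitator, coach and LIP measures. Report the deviation coefficient as the within-group association and the group-mean coefficient as the group-level association. Describe neither as a causal dose effect, because family self-selection remains. Keep any pooled correlation as descriptive only.

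The cost is one derived variable, one extra coefficient and slightly more complex reporting. No new data are needed if records carry a parenting-group identifier, which the mixed models for group nesting already require. If that identifier is unavailable, the split cannot be made and the report should say that the attendance association is pooled.

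The loss of precision is small. In the worked case the standard error of the within-group term is √[0.95/(50,000 × 0.747)] = 0.0050, against 0.0046 for the single slope, or about 9% larger before rounding.
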